### Outcomes

➢ Primary outcome: rate of DGF defined by the need for at least one dialysis session within the first 7 days after kidney transplantation➢ Secondary outcomes:○ Rate of SGF defined by a urine output of less than 1000 mL on day 1 after transplantation, or a decreased of less than 30 and 70% in creatinine plasma concentration, respectively, on days 3 and 7 after transplantation○ Combined rate of DFG + SGF○ Mild DGF defined by a serum creatinine reduction ratio from post-transplant day 1 to day 2 less than or equal to 30% plus 24-h urine creatinine excretion on day 2 greater than 1000 mg○ Severe DGF defined by a serum reatinine reduction ratio from post-transplant day 1 to day 2 less than or equal to 30% plus 24-h urine creatinine excretion on day 2 less than or equal to 1000 mg○ Duration of in-hospital length of stay (post-transplantation hospitalization)○ Daily urine output on days 1, 3 and 7○ Creatininemia and estimated creatinine clearance by the Modification of Diet in Renal Disease (MDRD) formula [17] on days 1, 3 and 7○ Rate of primary graft dysfunctions on day 1 defined by the absence of immediate renal function (anuria)○ Time between transplantation and normalization of graft function in patients presenting a DGF○ Function of kidney transplants at 1 year: kidney graft dysfunction defined by a clearance creatinine less than 30 mL min^−1^ estimated by the MDRD formula or total dysfunction defined by a persistent hemodialysis○ In-hospital and 1-year mortality rate of transplanted patients

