#### Sample size

The sample size was determined to obtain 80% power to detect a 10% difference for rate of DGF (as defined in the primary endpoint section) at day 7 between the two groups, as this difference is considered to be clinically significant. In accordance with previous studies [7, 8], we hypothesized that 30% of the patients in the placebo group and 20% of the patients in the intervention group will develop DGF. With the threshold for statistical significance set at a *p* value of 0.05 (two-sided alpha), these calculations showed that 588 participants (recipients) are needed (294 per group). Assuming that a potential 10% of participants will be lost to follow-up (for the primary or the secondary endpoints), a total of 648 recipients needs to be included. Secondary outcomes will be compared between the two groups: using the chi^2^ test or Fisher’s exact test for categorical variables and Student’s *t* test for continuous variables.

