### Data registration

Data will be entered into the web-based electronic Case Report Form (eCRF) (RedCap, Vanderbilt University, Nashville, TN, USA) by trial or clinical personnel under the supervision of the trial site investigators at each participating center. The following data reported to influence the outcome of kidney transplantation will be registered at the different stages of the procedure:➢ In donors with a beating heart:○ Demographic data (age, sex, Body Mass Index (BMI), ethnic group, cause of death)○ Significant medical history (chronic kidney disease, hypertension, diabetes, alcohol abuse)○ Detailed SOFA score in the last 24 h before organ harvesting○ Significant biochemical abnormalities: hypernatremia > 160 mmol L^−1^, coagulation abnormalities (disseminated intravascular coagulation)○ Renal function, assessed by blood urea nitrogen levels, creatininemia and 24-h creatinine clearance in the last 24 h prior to the harvesting○ Immunological and viral status: Epstein-Barr virus (EBV) serology, number of HLA incompatibility➢ During kidney harvesting, preservation and transplantation○ Preservation data: type of preservation solution, use of a perfusion machine, cold ischemia time○ Intraoperative data: hemodynamic stability (systolic blood pressure < 80 mmHg, need for vasopressors), warm ischemia time, technical problems (duration of anastomose, surgical difficulties, hemorrhage)➢ In transplanted patients○ Demographic data (age, sex, BMI, blood group, ethnic characteristic)○ Significant medical history: hypertension, cardiac failure, diabetes, cause of the kidney disease, previous transplantation(s), duration of dialysis before transplantation, duration on the transplantation waiting list○ Viral (C hepatitis) and immunological (anti-donor antibodies) status○ Dialysis during the first week after transplantation○ Creatininemia and estimated creatinine clearance (MDRD) on days 1, 3 and 7 after transplantation○ 24-h urine output on days 1, 3 and 7 after transplantation○ Recipient and graft survival at 1 year

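### Time to normalization of graft function is assigned to a t test, which has no place for recipients who never recover, and the listed data do not date a recovery after day 7

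*Protocol article*

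**What the plan says.** The Outcomes section of the protocol article lists among its secondary outcomes "Time between transplantation and normalization of graft function in patients presenting a DGF". It gives no criterion for normalization and no time horizon. The population follows from the primary outcome, "rate of DGF defined by the need for at least one dialysis session within the first 7 days after kidney transplantation", so every recipient in this comparison was dialysed in the first week.

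The same section foresees recipients who do not recover. One 1-year outcome begins "Function of kidney transplants at 1 year: kidney graft dysfunction defined by a clearance creatinine less than 30 mL min" and goes on to define total dysfunction as hemodialysis that persists. In-hospital and 1-year mortality form a further outcome.

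The tests for secondary outcomes are in the last sentence of the Sample size section: chi-square or Fisher's exact test for categorical variables, and "Student’s *t* test for continuous variables". No other method is stated for this outcome.

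The Data registration section lists the recipient items on dialysis and graft function. The dialysis item reads "Dialysis during the first week after transplantation". Serum creatinine with its MDRD clearance, and the daily urine volume, are each to be recorded at days 1, 3 and 7. The only later item in the list is "Recipient and graft survival at 1 year".

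**The concern.** A time to recovery is not an ordinary continuous variable. Some recipients reach the event, some are still waiting at the end of follow-up, and some die or lose the graft first. A t test compares means and needs a number for every recipient it includes, so those without a time are either left out or given an invented value. They are the worst cases in a comparison meant to describe how long graft dysfunction lasts, and treatment may change how many of them fall in each arm.

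The second worry is the data. If only the listed items were available, every recovery after day 7 would also lack a time. The t test would then rest on recipients who recovered within the week, and its direction could mislead. A treatment that shortened recovery from 20 to 10 days would add no dated value. A treatment that moved recoveries from day 10 to day 7 would add long values to its own arm and make that arm look slower.

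**Working it through.** **Step 1. Reproduce the plan's figure.** Inputs from the Sample size section: 30% versus 20% DGF, two-sided alpha 0.05, power 80%, 1:1 allocation. The pooled-variance formula without continuity correction is

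n = [1.960 × √(2 × 0.25 × 0.75) + 0.842 × √(0.30 × 0.70 + 0.20 × 0.80)]² / 0.10² ≈ 293.2, rounded up to 294 per group.

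This gives 588 in total, as stated (power at 294 per group: 0.801). Adding 10% gives 294 × 1.10 = 323.4, or 324 per group and 648 in total, as stated. The point disputes neither figure.

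**Step 2. Expected number in this comparison.**

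- Evaluable: 0.30 × 294 + 0.20 × 294 = 88.2 + 58.8 = 147 of 588.
- Enrolled: 0.30 × 324 + 0.20 × 324 = 97.2 + 64.8 = 162 of 648.

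**Step 3. Which DGF recipients have a value for a t test?**

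| Course of the recipient | With the listed items only | If the eCRF also holds a recovery date |
|---|---|---|
| Recovers by day 7 | Value available, at the resolution of the week-one data | Value available |
| Recovers between day 7 and 1 year | Known only to lie in that interval | Value available |
| Still on hemodialysis at 1 year | No value exists | No value exists |
| Dies without recovery | No value exists | No value exists |

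The last two rows are the same in both columns. A better case report form repairs the second row only. The last two need a different method.

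**Step 4. Size of the second row.** The documents do not give the share of DGF recipients who recover after day 7. The range below is an assumption.

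| Assumed share | Of 147 | Of 162 |
|---|---|---|
| 10% | 15 | 16 |
| 30% | 44 | 49 |
| 50% | 74 | 81 |
| 70% | 103 | 113 |

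The documents also give no rate of persistent hemodialysis or death among DGF recipients, so the last two rows of the Step 3 table cannot be counted.

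**The case against.** The strongest reply is that the list under Data registration is not the full case report form. It is introduced as data known to influence the transplant result. It omits items that other stated outcomes need: day-2 serum creatinine, day-2 urine creatinine excretion, length of stay and 1-year clearance. Figure 1, the overview of assessments, is not shown. A journal article condenses, and a recovery date is the kind of field it may leave out. This stands. A reader might infer that recovery after day 7 cannot be observed in this trial, but the documents do not support that. They show only that the listed items do not date it.

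A reader might also infer that dialysis and renal function are recorded in the first week and never again. That is not so, because the 1-year outcome uses estimated clearance and hemodialysis status. Those data show whether a graft works at 1 year, but not when it began to. Nor can one say that week-one recoveries fall only on the measurement days, since dialysis sessions may be recorded by date.

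A further reply is that the sentence on tests is generic and that censoring rules belong in a statistical analysis plan, which is not shown. This stands in part. The sentence does not name this outcome, and a later plan may refine it. But the article does state a method for continuous secondary outcomes, gives no other for this one, and itself foresees recipients to whom that method cannot apply.

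Finally, this is one of many secondary outcomes and is not among the main secondary objectives named in the Background. That is correct and limits the weight of the point.

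**Conclusion.** The point holds in a limited form. The stated t test does not suit time to normalization, because recipients who die without recovery or remain on hemodialysis have no time to analyse. This conclusion does not depend on what the eCRF contains. The data gap after day 7 is conditional: it is real on the items the article lists, and disappears if the eCRF records a recovery date.

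The comparison would involve about 147 evaluable DGF recipients at the planned rates. Between 15 and 103 of them would lack a dated recovery if the listed items were all there is and if 10% to 70% recover after day 7. At the low end the loss is modest. From 30% upward it is at least 44 of 147, and these would be the prolonged cases. The reversal of direction described above likewise applies only if no later recovery date exists.

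The change is worth making, but it concerns one secondary outcome.

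**What to change.** Replace the t test for this outcome with a time-to-event comparison from transplantation to 1 year. Handle death and graft loss without recovery, including hemodialysis persisting at 1 year, under one rule: either all count as not recovered through 1 year, or all count as competing events. A single rule matters because the Outcomes section classes persistent hemodialysis as total graft dysfunction, so separate rules for the two could give one recipient two codes.

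State the criterion for normalization. Confirm that the eCRF holds a dated item that matches it, and add one if it does not. One candidate is the date of the last dialysis session of the initial DGF episode. The field should say so explicitly, so that a later return to dialysis after an early recovery does not overwrite the date.

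The cost is one amended analysis line and at most one date field. If dialysis independence is used as the criterion, the drawback is that it is narrower than normalization of graft function, and the outcome should then be named accordingly. If the date is already collected, only the outcome and analysis text change.

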## Abstract

**Background:**

Renal transplantation represents the treatment of choice of end-stage kidney disease. Delayed graft function (DGF) remains the most frequent complication after this procedure, reaching more than 30%. Its prevention is essential as it impedes early- and long-term prognosis of transplantation. Numerous pharmacological interventions aiming to prevent ischemia-reperfusion injuries failed to reduce the rate of DGF. We hypothesize that cyclosporine as an early preconditioning procedure in donors would be associated with decreased DGF.

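### Time to normalisation of graft function is compared only among recipients with DGF, a post-randomisation subgroup the drug is meant to shrink, so the comparison can mislead

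*Protocol article*

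**What the plan says.** The Outcomes section of the protocol article includes, among the secondary outcomes, "Time between transplantation and normalization of graft function in patients presenting a DGF". The same section defines the condition for entering that comparison as the trial's primary endpoint: "Primary outcome: rate of DGF defined by the need for at least one dialysis session within the first 7 days after kidney transplantation".

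The Abstract gives the direction of the expected effect: "We hypothesize that cyclosporine as an early preconditioning procedure in donors would be associated with decreased DGF". The Sample size section puts numbers on it: "we hypothesized that 30% of the patients in the placebo group and 20% of the patients in the intervention group will develop DGF". That section also says that secondary outcomes are to be compared between the groups, with "Student’s *t* test for continuous variables".

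The article does not define this outcome in all recipients, does not label it as descriptive, and does not adjust for selection into the DGF subgroup.

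**The concern.** Randomisation makes the groups comparable at the time of allocation. Membership of the DGF subgroup is settled up to 7 days after transplantation, and so after the donor was treated. If the trial's hypothesis is true, the placebo DGF cases include recipients whose counterparts on cyclosporine never developed DGF. A between-group difference in recovery time then mixes any effect on recovery with a change in who is being compared.

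The direction of the distortion depends on which cases are prevented. If they are mostly the milder ones, the treated DGF cases are on average more severe and their recovery looks slower. A trial with a positive primary result could then report a secondary finding of delayed recovery that reflects selection alone. If the drug also shortens recovery, the same restriction can hide most of that benefit.

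**Working it through.** **1. The plan's own figure.** Inputs from the Sample size section: 30% and 20%, two-sided alpha 0.05, power 80%. With the pooled-variance formula without continuity correction, and mean proportion 0.25:

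n = [1.960·√(2·0.25·0.75) + 0.842·√(0.30·0.70 + 0.20·0.80)]² / 0.10² = (1.200 + 0.512)² / 0.01 ≈ 293.2, rounded up to 294 per group.

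This matches "588 participants (recipients) are needed (294 per group". The sample size is not in question.

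**2. Who enters the restricted comparison.** Placebo: 294 × 0.30 = 88.2, about 88. Cyclosporine: 294 × 0.20 = 58.8, about 59. On the design rates, 10 of every 30 placebo-type DGF cases (one third) do not occur on treatment.

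**3. A small example (assumed durations).** Per 100 placebo recipients, suppose 20 DGF cases are mild (8 days to recovery) and 10 severe (20 days).
- Placebo mean: (20·8 + 10·20)/30 = 12.0 days.
- The drug prevents 10 mild cases and changes nothing else. Treated mean: (10·8 + 10·20)/20 = 14.0 days.

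The DGF-only mean is 2 days worse although no recipient recovered later. With 7 and 14 days the gap is 10.5 − 9.3 = 1.2 days. With 10 and 25 days it is 17.5 − 15.0 = 2.5 days.

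**4. How often a t test would call this harm.** Assumptions: 88 against 59 cases; one third of DGF prevented in every scenario; durations exponential, or lognormal with log-SD 0.7; recipients treated as independent. Short and long are split at the median, so prevention probabilities are 4/9 and 2/9 for a 2:1 ratio, and 1/2 and 1/6 for 3:1. There were 20,000 simulated trials per row.

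| Which DGF cases are prevented | Mean in treated DGF cases, exponential / lognormal | Significant apparent harm, exponential / lognormal |
|---|---|---|
| Unrelated to duration | unchanged | about 3% / 3% (nominal) |
| Short twice as often as long | +12% / +9% | about 11% / 10% |
| Short three times as often | +17% / +13% | about 18% / 16% |
| Exactly the shortest third | +41% / +31% | 67% / 63% |
| Shortest third, remaining episodes 20% shorter | +13% / +5% | about 12% / 6% |

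The fourth row can be checked by hand for the exponential case. With mean 1 and truncation below the 1/3 quantile, the mean is 1 − ln(2/3) = 1.405. Then z = 0.405/√(1/59 + 1/88) = 0.405/0.168 = 2.41, and power is Φ(2.41 − 1.96) = 0.67. Repeat runs move the entries by about one percentage point.

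**5. A second model.** Here time from transplantation is lognormal in all recipients, with log-SD 0.5 to 1.0, and DGF is taken as the 30% of placebo recipients above 7 days.
- Mildest third prevented: the DGF-only mean rises from 10.0 to 11.2 days (log-SD 0.5) or from 15.5 to 19.2 days (log-SD 1.0). Significant apparent harm occurs in 66% and 46% of trials, while the mean over all recipients improves (6.1 to 5.8 and 6.8 to 6.5 days, with prevented cases set to 5 days).
- Everyone's recovery shortened by the same factor (15% to 27%, enough to bring DGF to 20%): the DGF-only mean falls by only 4% to 10%. Significant benefit appears in 11% to 14% of trials and apparent harm in under 0.5%. This is dilution without reversal.

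**The case against.** The strongest reply is that reversal needs a particular pattern of effect. The figure of about two thirds requires the drug to remove exactly the shortest DGF episodes and to leave all others untouched. The article gives no recovery times or severity mix to support that. Its Background section cites an animal model in which cyclosporine reduced the degree of organ dysfunction, which suggests a graded effect, and under a uniform shortening there is no reversal. This stands. It limits the size of the problem but does not restore a randomised comparison: even in the uniform case the DGF-only contrast shows only part of the benefit.

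A reader might also infer that recipients who die or never recover are dropped, because a t test needs a value for each of them. The article does not say so. The t-test sentence is a general line covering every continuous secondary outcome, the Data analysis section plans normality checks, and the handling of non-recovery is a detail that a condensed article may leave to the full protocol or analysis plan. Persistent haemodialysis at 1 year and mortality are also outcomes in their own right. That inference forms no part of this point.

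Finally, how long DGF lasts once it occurs is a legitimate clinical question, and this is one item in a long secondary list. Both are true. They argue for keeping the figure as description, not for testing it between groups.

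**Conclusion.** The point holds for one secondary outcome. The restriction to DGF cases is part of the published outcome definition, and the between-group comparison is stated, so this is not a gap left to a later document. The comparison lacks the protection of randomisation whenever the drug affects DGF, which is the trial's hypothesis.

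The size cannot be fixed from the article. Under the stated assumptions, significant apparent harm ranges from the nominal 3% or so, through about 10–17% with moderate selection of short episodes, to about 63–67% at the extreme. A uniform effect produces dilution. It would go too far to conclude that the outcome is bound to be biased or that an effective drug would look harmful: if prevention is unrelated to duration, there is no distortion. What the article supports is that the result can mislead, and that its data could not show which case applies. The primary analysis, the sample size and the secondary outcomes measured in all recipients are unaffected.

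**What to change.** Before unblinding, state that duration among recipients with DGF is reported by group as description only, with no between-group p value and no causal interpretation. This costs one sentence.

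If a randomised comparison of recovery time is wanted, define it in all transplanted recipients of the full analysis population. Recipients without DGF take the shortest time or rank. Death and permanent graft failure are handled as competing events or as worst rank. The event should remain normalisation of graft function, with its criterion stated; if dialysis-free function is used in its place, say that this is a different outcome. Acknowledge also that the all-recipient version partly repeats the primary result, since on the design rates 70% to 80% of recipients would share the best value. The cost is a little more analysis work and recording the date of recovery or of last dialysis in the eCRF. The number of recipients does not change.

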**Methods:**

The Cis-A-rein study is an investigator-initiated, prospective, multicenter, double-blind, randomized, controlled study performed to assess the effects of a donor preconditioning with cyclosporine A on kidney grafts function in transplanted patients. After randomization, a brain dead donor will receive 2.5 mg kg^−1^ of cyclosporine A or the same volume of 5% glucose solution. The primary objective is to compare the rate of DGF, defined as the need for at least one dialysis session within the 7 days following transplantation, between both groups. The secondary objectives include rate of slow graft function, mild and severe DGF, urine output and serum creatinine during the first week after transplantation, rate of primary graft dysfunction, renal function and mortality at 1 year. The sample size (*n* = 648) was determined to obtain 80% power to detect a 10% difference for rate of DGF at day 7 between the two groups (30% of the patients in the placebo group and 20% of the patients in the intervention group).

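### Kidney function at 1 year is assessed only by a cut at MDRD clearance below 30 mL/min or hemodialysis; the full-scale value should be added as an outcome beside it

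*Protocol article*

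**What the plan says.** The Abstract (Methods) lists "renal function and mortality at 1 year" among the secondary objectives, and the Background names graft function at 1 year among the main ones.

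Under Outcomes, the 1-year item reads "kidney graft dysfunction defined by a clearance creatinine less than 30 mL min^−1^ estimated by the MDRD formula or total dysfunction defined by a persistent", and its last word is hemodialysis. No other function outcome at 1 year is listed; 1-year mortality is a separate item. In the same list, clearance is an outcome on its measured scale only in the first week: "Creatininemia and estimated creatinine clearance by the Modification of Diet in Renal Disease (MDRD) formula [17] on days 1, 3 and 7".

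The last sentence of the Sample size section says how secondary outcomes are compared: "using the chi^2^ test or Fisher’s exact test for categorical variables and Student’s *t* test for continuous variables". A dysfunction rate is categorical, so it falls to chi-square or Fisher.

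The Data registration section lists "Creatininemia and estimated creatinine clearance (MDRD) on days 1, 3 and 7 after transplantation". At 1 year it lists only survival of the recipient and of the graft.

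**The concern.** To apply the cut, an MDRD value must be obtained at 1 year for every recipient with a functioning graft. That value is then reduced to which side of 30 mL/min it falls on. Reading the item as two grades (partial and total dysfunction) does not change this, because everyone at or above 30 is still in one class. The protocol gives no reason for the threshold, and no reason why the measured scale is used in the first week but not at 1 year.

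Long-term function is central to the trial's rationale. The Background calls its alteration the main problem that follows from delayed or slow graft function, and the Discussion says DGF worsens long-term prognosis. If treatment moved 1-year clearance moderately across recipients, the listed outcome could well show no difference where the measured values would have shown one.

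**Working it through.** **The plan's own figure.** The only sample size calculation is for DGF at 30% v 20%, two-sided alpha 0.05, power 80%:

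n = [1.96·√(2·0.25·0.75) + 0.842·√(0.30·0.70 + 0.20·0.80)]² / 0.10² = (1.200 + 0.512)² / 0.01 ≈ 293.1, so 294 per group and 588 in total.

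This agrees with the plan. No rate, SD, effect or power is given for 1-year function, so the inputs below are assumptions, apart from 294 per arm and the DGF rates. Recipients are treated as independent; two kidneys from one donor would lower the power of both analyses.

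**Information kept by the cut under a uniform shift.** For normal clearance with mean m and SD s, let z = (30 − m)/s and p = Φ(z). The efficiency of the cut relative to the full scale is φ(z)² / [p(1 − p)].

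| m | s | p below 30 | efficiency |
|---|---|---|---|
| 45 | 20 | 22.7% | 0.52 |
| 45 | 15 | 15.9% | 0.44 |
| 50 | 18 | 13.3% | 0.40 |
| 55 | 20 | 10.6% | 0.35 |
| 55 | 15 | 4.8% | 0.22 |

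The efficiency falls below one half when p is about 21% or less. It is 0.58 at p = 30% and at most 0.64 (p = 50%).

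**Power with complete data (m = 50, s = 18, 294 per arm).** The standard error on the full scale is 18·√(2/294) = 1.485. For a 4 mL/min shift, 4/1.485 = 2.69 and the power is Φ(2.69 − 1.96) = 77%. For the cut, the proportions are Φ(−20/18) = 13.3% and Φ(−24/18) = 9.1%, and the power is 36%. Shifts of 3 and 5 mL/min give 52% v 23% and 92% v 51%. For 1 mL/min it is about 10% v 6%, so neither analysis is useful.

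**Power of the analysis proposed here (simulated).** Here 6% of each arm has lost the graft and takes the lowest rank. Wilcoxon is compared with uncorrected chi-square on clearance below 30 or lost graft.

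| uniform shift (mL/min) | rank test | cut |
|---|---|---|
| 3 | about 42% | 17% |
| 4 | about 64% | 26% |
| 5 | about 81% | 35% |

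At 264 per arm (294 less 10%), the 4 mL/min case gives 61% v 24%.

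**Effect solely through DGF.** The plan assumes that DGF falls by 10 percentage points. If avoiding DGF is worth 10 mL/min at 1 year, the mean shift is 0.10 × 10 = 1 mL/min; a mean shift of 4 would need 40 mL/min per case avoided. Simulation with DGF 30% v 20%, mean 52 without DGF, SD 18 and 6% graft loss in both arms gives rank test v cut of about 8% v 7%, 13% v 10% and 19% v 15% for DGF penalties of 10, 15 and 20 mL/min.

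**Effect on graft loss only.** With no shift and loss of 10% v 5%, simulations gave 15% to 18% for the rank test and 25% to 27% for the cut. With 9% v 3% it is about 24% v 37%.

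**The case against.** The strongest objection is that the uniform shift is not the mechanism the protocol describes. Its argument is that preventing DGF protects later function. On that path only the 10% of recipients whose DGF status changes can benefit, and the full scale then gains about 1 to 4 points of power, with both analyses weak. If the benefit is a reduction in graft loss, the binary outcome is the better test, because it captures hemodialysis directly. A threshold for severe dysfunction is also a legitimate clinical endpoint. This all stands. It means the cut should remain a tested outcome.

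It does not remove the point. The protocol does not say that any effect is confined to DGF or to graft loss, and no single scenario can be assumed in advance. Reporting both outcomes covers them.

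A second objection is that an article may leave a measured-scale analysis to the full protocol or the SAP. An SAP could add one. But the article does not leave 1-year function open: it defines the outcome and states the kind of test, and that stated choice is what is questioned.

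Third, clearance is undefined for recipients on dialysis or dead, so a full-scale analysis needs explicit rules. That is correct, and the fix supplies or asks for them.

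A reader might infer that the plan is shown to discard half or more of the information. The documents do not support that as an unconditional statement. It needs a 1-year dysfunction rate of about 21% or less, roughly normal clearance and a shift common to all recipients, and the protocol gives none of these.

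**Conclusion.** The point holds in a limited form. The protocol fixes 1-year function as a single low threshold and keeps no measured-scale outcome beside it, although renal function at 1 year is a stated objective. Under a uniform shift, with the assumed distributions, the cut keeps 22% to 52% of the information. With 6% graft loss it costs roughly 25 to 46 points of power for shifts of 3 to 5 mL/min. The cost is close to nil if the effect acts only through DGF, and it reverses if the effect is on graft loss alone. The case therefore rests on cheap protection against missing a broad shift, not on a demonstrated loss. This is a secondary outcome, and neither the primary analysis nor the 588 or 648 recipients are affected. The change is worth making.

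**What to change.** 1. Under Outcomes, add full-scale MDRD clearance at 1 year as a secondary outcome. Keep the existing binary outcome, and keep it tested.
2. In the analysis text, compare the new outcome with a rank-based test in which recipients whose graft has failed or who are on persistent hemodialysis take the lowest rank. State in advance how deaths with a functioning graft are ranked.
3. Report the between-group difference in clearance, with a 95% confidence interval, among recipients with a functioning graft. Label it descriptive, because that subset is defined after randomization.
4. Under Data registration, list creatinine and MDRD clearance at 1 year. They are absent there, although the current binary outcome already cannot be derived without them.

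The cost is a few sentences and one data item that the present definition already needs, with no extra patients. The downsides are one more secondary comparison and a rank result that is less directly clinical than a proportion, which is a further reason to keep the proportion.
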